#### Sample

The sample includes 36 sites, with each site composed of one JJ and one or two BH agencies (overall more than 72 participating organizations). Sites were matched into pairs within state systems (based on local population, number of youth referred to JJ, number of staff, and whether EBPs are used). JJ agencies include probation departments (in six states) or drug courts (in one state); BH providers include substance use treatment providers within a county or service region. JJ inclusion criteria were (a) ability to provide youth service records, (b) serve youth under community supervision, (c) access to treatment provider(s) if treatment is not provided directly, (d) minimum average case flow of 10 youth per month, (e) minimum of 10 staff per site, and (f) a senior JJ staff member who agrees to serve as site leader/liaison during the study. Study sites are geographically dispersed and were identified by state JJ agencies (and not selected for particular substance use or related BH service needs).

At the beginning of the project, each site forms an *Interagency Workgroup* composed of 8–10 representatives from JJ and BH agencies. Recommended composition includes representatives of JJ leadership (e.g., Chief Probation Officer), BH leadership (e.g., Program Director), other JJ and BH agency staff, and other key stakeholders likely to be involved in improvement efforts (e.g., Juvenile Court Administrator, JJ Data Manager).

At least 360 staff members from participating JJ and BH agencies are expected to participate in one or more study activities. Information from at least 120 individual youth case records per site is de-identified and extracted from site data files on a quarterly basis throughout the study period (a minimum sample of 4320 de-identified service records). Interagency workgroup participation, staff survey responses, and youth records are nested within sites.

#### Recruitment and consenting

Partners facilitated identification and recruitment of JJ agencies. RC staff described study involvement and worked with JJ leadership to identify and recruit the BH partner. JJ agency leadership provided signed letters of commitment and, if required by agency policy or state law, court orders authorizing RC access to confidential juvenile case records. Individual staff recruitment occurs immediately after each leadership and line staff orientation meeting. During orientations, all aspects of the research study are explained and informed consent is obtained from participants, consistent with institutional review board (IRB) protocols at each RC.

#### Randomization

The design features two stages of randomization: (a) to one of three start times as part of a phased rollout and (b) to the Core or Enhanced condition. The CC was responsible for all randomization procedures. For the first stage, RCs were used as strata and the six county sites within each were matched into pairs in terms of the number of youth (ages 10–19) in the county based on the 2010 census, the number of youth entering community supervision, the number of staff in community supervision, whether they used standardized screeners/assessments and evidence-based treatment. Each RC PI reviewed matches and ensured comparability prior to randomization. Within each RC, the three resulting pairs were then randomly assigned to one of three start times using a random number generator in Excel. This procedure was utilized to smooth out the logistical burden of implementation and to control for the influence of other exogenous factors [63, 64].

For the second stage of randomization, one site in each pair was randomly assigned to Core and the other to Enhanced. Given that there were only 18 pairs of sites, “optimal” randomization was used to find the most balanced pattern of assignment across each RC. This approach involved running 10,000 permutations of the possible assignments of sites within each pair to condition. For each of these, multivariate Hotelling’s *T*
^2^ was computed to assess the degree of balance on cohort and condition both within and across all RCs. The final randomization design was selected from a pool of the top 2 % of permutations balancing across all characteristics.

The study is also double-blinded such that neither the RC staff nor any county site staff are aware of their assignment until after both sites in a pair have completed the Core components. Once completed, the condition of both sites is revealed by the CC PI to RC PI and, subsequently, to sites. This design aspect is ideal in studies with multiple sites that have initial variability and require intensive researcher-driven activities such as training, monitoring, or coaching.

#### Power

For service record level hypotheses, 2160 bi-weekly observations are expected on service delivery outcome measures (36 sites × 60 bi-weekly periods). For site-level hypotheses, 72 observations are expected (36 sites × 2 data collection points), and for staff level hypotheses, a minimum of 1440 observations are expected, with 720 per condition (average of 10 staff × 36 sites × 4 time points). The effective *n* for power calculations in repeated measures analysis varies between a lower bound of the number of unique sites (*N* = 36) and an upper bound of the observations per condition (*O* = 1440 staff surveys or 2160 bi-weekly youth record periods), as a function of the Intraclass Correlation Coefficient (ICC) associated with the outcome measure (e.g., number of youth entering treatment) over time and the number of repeated measures per site. Assuming that the ICC is low (.2 or less), effect sizes in the small to moderate range (.25 to .35) should be detected with 80 % or more power [65]. Several strategies are employed to further increase power: (a) optimal randomization to evenly distribute the 36 sites as much as possible across start up time and condition, (b) using standardized measures to reduce measurement error, and (c) modeling site differences as a function of staff and organizational covariates.

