### Measurement

A multilevel approach to measurement is necessary for our understanding of change processes within complex service systems [36, 66]. Youth interact with JJ agency staff who work within a larger organization; in turn, the organization operates within a system that includes BH providers, oversight agencies, and funders. The proposed measurement plan assesses information from these levels.

The design employs three data collection periods: baseline (6 months; generally corresponding to EPIS’ Exploration and Preparation phases), experiment (12 months; corresponding to EPIS’ Implementation phase), and post-experiment (6 months; corresponding to EPIS Sustainment phase). Figure 4 includes a timeline depicting all intervention components (top portion) and data collection (bottom portion) for sites in wave 1. During baseline, RCs initiate collection of de-identified youth records data related to the Cascade dating back to October 1, 2014, administer agency surveys, conduct a local needs assessment (systems mapping exercise and group interview with interagency workgroup members), and administer leadership and line staff surveys at participating agencies. Leadership and line staff complete follow-up surveys during months 2 and 12 of the experiment period and again at month 6 of the post-experiment period. A representative from each site reports progress toward site-selected goals (i.e., implementation activities) during a monthly site check-in phone call. In the Enhanced condition, local change team members complete implementation process surveys during the experiment period. The 6-month post-experiment period consists only of data collection, including youth record extraction, agency and staff surveys, group interview (to determine whether sites sustain new practices), and monthly site check-in calls. Data collection components are summarized in Table 2.

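### The Power paragraph labels both-condition totals as per-condition counts, and under its own effective-n method .35 is not detectable with 80% power at ICC .2 in a Core-versus-Enhanced comparison

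*Protocol article*

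**What the plan says.** All of this is in the Power section under Study design.

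- **Records:** "2160 bi-weekly observations are expected on service delivery outcome measures", from 36 sites and 60 periods.
- **Staff:** "a minimum of 1440 observations are expected, with 720 per condition", built from an "average of 10 staff × 36 sites × 4 time points".
- **Site level:** "72 observations are expected", from 36 sites and two data collection points.
- **Effective n:** it lies between the number of unique sites (36) and an "upper bound of the observations per condition", given as 1440 or 2160. Where it falls depends on the ICC and on the number of repeated measures per site.
- **Claim:** "Assuming that the ICC is low (.2 or less"), "effect sizes in the small to moderate range (.25 to .35) should be detected with" at least 80% power.

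The section does not state alpha, sidedness or the contrast being powered.

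**The concern.** The section gives 1440 as the staff total, 720 in each condition, and then uses 1440 as a per-condition count. The 2160 record periods come from all 36 sites, 18 Core and 18 Enhanced, so that figure is also a total. The lower bound of 36 likewise counts both conditions.

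A factor of two in n per condition changes a detectable effect by a factor of about 1.4. That is enough to move the result across the upper end of the stated range. Core versus Enhanced is the head-to-head question of the trial, and readers will use the stated range to judge what a null result rules out.

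**Working it through.** **Inputs.** From the Power section: 36 sites; 60 record periods per site; 10 × 4 = 40 staff observations per site; ICC .2; target effects .25 and .35; power 80%. From Main trial: 18 sites per condition. Assumed, because not stated: two-sided 5%, so z = 1.960 + 0.842 = 2.802.

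**Effective n.** The stated bounds (36 at ICC 1, all observations O at ICC 0) are those of

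n_eff = O / (1 + (m − 1) × ICC), with m = 60 (records) or 40 (staff).

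Minimum detectable effect (MDE) = 2.802 × √(2 / n_eff per condition).

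**Attempt to reproduce the stated range (ICC .2, totals used as per-condition n)**
- Records: 2160 / 12.8 = 168.8; MDE = 2.802 × √(2/168.8) = .305.
- Staff: 1440 / 8.8 = 163.6; MDE = 2.802 × √(2/163.6) = .310.

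Both lie inside .25 to .35, although power at .25 is still only 63% and 62%.

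**Correct per-condition counts (ICC .2)**

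| | Records | Staff |
|---|---|---|
| Observations per condition | 1080 | 720 |
| Design effect | 1 + 59 × .2 = 12.8 | 1 + 39 × .2 = 8.8 |
| Effective n per condition | 84.4 | 81.8 |
| MDE at 80% power | .431 | .438 |
| Power at .35 | 62% | 61% |

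One-sided 5% gives .383 and .389, still above .35. More observations per site cannot close the gap: as m grows without limit, the MDE with 18 sites per condition tends to 2.802 × √(2 × .2/18) = .418.

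**ICC at which the claim holds.** Required effective n per condition is 2 × (2.802/δ)², which is 129 for δ = .35 and 252 for δ = .25. Solving 1080/(1 + 59 × ICC) and 720/(1 + 39 × ICC) for these values gives:
- .35: ICC up to .125 (records) or .117 (staff).
- .25: ICC up to .056 (records) or .048 (staff).

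**Site level.** With 36 observations per condition, all independent, MDE = 2.802 × √(2/36) = .66. At ICC .2 with m = 2, n_eff is 72/1.2 = 60, or 30 per condition, and the MDE is .72.

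**Alternative contrast: Core-versus-Enhanced difference in change from baseline.** Assume compound symmetry and no site-by-period variance. With a baseline and b later observations per site, MDE = 2.802 × √(2 × (1 − ICC) × (1/a + 1/b) / 18).
- Records, 13 baseline and 26 experiment periods: .28 at ICC .2, .32 at ICC 0.
- Records, about 33 baseline and 26 experiment periods (using records back to October 2014): .22 at ICC .2.
- Staff H4a, baseline versus end of experiment, 10 and 10: .37 at ICC .2, .42 at ICC 0.

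**The case against.** The strongest reply is that H1 and H2 are about change from baseline, not about levels. A difference-in-change contrast removes the stable site effect, and for records it gives about .22 to .28 at ICC .2 without any doubling. Before-after comparisons for H1 over all 36 sites do better still, at about .14 to .19. This stands as a statement about what the trial might detect, if site-by-period variance is negligible. It does not rescue the paragraph. In that contrast a lower ICC makes the MDE larger, whereas the paragraph makes its claim conditional on a low ICC. Nor does it bring the two-wave staff comparison in H4a within .35. Comparing baseline with all three later staff waves would give about .31, and the plan allows growth modelling, but H4a is worded as baseline to end of experiment.

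A second reply is that a range of effects paired with a range of ICCs need not promise .25 at ICC .2. That is fair, so the test here is .35 at ICC .2, which still fails.

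A third is that a staff design effect based on 10 staff per site, with the four waves treated as independent, gives 720/2.8 = 257 per condition and an MDE of .25. That contradicts the stated lower bound of 36. Matching and covariates may also add power, but the section puts no figure on either.

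Four stronger readings are tempting and not supported:
- **That the totals must have been used as per-condition n.** The article does not show its calculation. Doubling puts the ICC .2 figure inside the range, but it is not the only route there.
- **That H1 and H2 have poor power.** The 61-62% belongs to an unadjusted comparison of levels between conditions.
- **That 60 record periods is too many.** The Measurement section says "The design employs three data collection periods: baseline (6 months") followed by a 12-month experiment, which suggests about 39 periods. But records reach back to October 1, 2014. To the end of month 19 that is about 54, 59 and 63 periods for waves 1 to 3, so 60 is consistent.
- **That the range is claimed for site-level hypotheses.** The 72 observations are not in the effective-n sentence, and H3b and H3c are labelled largely descriptive and exploratory. The text merely fails to exclude them.

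**Conclusion.** The concern holds in a limited form. The per-condition labels on 1440 and 2160 contradict the same paragraph; the correct counts are 720 and 1080. Under the effective-n approach described there, the upper end of the range is missed at ICC .2: the MDE is about .43 to .44 instead of at most .35. The .35 claim is good to an ICC of about .12, not .2.

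This rests on two-sided 5%, equal allocation, and an effective-n formula inferred from the two stated bounds. It shows that the stated figure does not follow from the stated method. It does not show that the trial is too small for H1 or H2, because their sensitivity depends on a change contrast and on site-by-period variance, which the section does not address.

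**What to change.** 1. Replace the upper bounds with 720 staff surveys and 1080 record periods per condition, and give the lower bound on the same basis (18 sites per condition).
2. State alpha, sidedness and the contrast being powered.
3. Then do one of the following. Either keep the described method and restate the detectable effect as about .43 (records) and .44 (staff) at ICC .2, or limit the .35 claim to an ICC of about .12. Or recompute for the difference in change from baseline, state the assumption about site-by-period variance, and quote records and staff separately.
4. Say that the range does not apply to the 72 site-level observations.

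The cost is a few sentences and a recalculation. No sites, data collection or analyses change. If the described method is kept, the quoted sensitivity becomes less favourable.

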### Measurement

A multilevel approach to measurement is necessary for our understanding of change processes within complex service systems [36, 66]. Youth interact with JJ agency staff who work within a larger organization; in turn, the organization operates within a system that includes BH providers, oversight agencies, and funders. The proposed measurement plan assesses information from these levels.

The design employs three data collection periods: baseline (6 months; generally corresponding to EPIS’ Exploration and Preparation phases), experiment (12 months; corresponding to EPIS’ Implementation phase), and post-experiment (6 months; corresponding to EPIS Sustainment phase). Figure 4 includes a timeline depicting all intervention components (top portion) and data collection (bottom portion) for sites in wave 1. During baseline, RCs initiate collection of de-identified youth records data related to the Cascade dating back to October 1, 2014, administer agency surveys, conduct a local needs assessment (systems mapping exercise and group interview with interagency workgroup members), and administer leadership and line staff surveys at participating agencies. Leadership and line staff complete follow-up surveys during months 2 and 12 of the experiment period and again at month 6 of the post-experiment period. A representative from each site reports progress toward site-selected goals (i.e., implementation activities) during a monthly site check-in phone call. In the Enhanced condition, local change team members complete implementation process surveys during the experiment period. The 6-month post-experiment period consists only of data collection, including youth record extraction, agency and staff surveys, group interview (to determine whether sites sustain new practices), and monthly site check-in calls. Data collection components are summarized in Table 2.

**Fig. 4 Fig4:**
[figure not shown]
Timeline depicting intervention components (*top portion*) and data collection (*bottom portion*) for sites in wave 1

**Table 2 Tab2:** Data collection components

Instrument	Description	Timing	Participant investment
START UP			
Pre-implementation checklist	Documents, orientations, memos of understanding, necessary approvals.	Month 1 (baseline)	Research staff; 1 h
INTERVENTION ACTIVITIES			
Core components			
Needs assessment group interview	Staff focus group (audio recorded and transcribed) designed to explore existing services along the Cascade, identification of strengths and gaps in services, creation of systems map; documentation of inner and outer context	Month 3 (baseline), month 21 (post-experiment)	Research staff; interagency workgroup (JJ and BH staff); 3 h
Site feedback report fidelity checklist	Documents the degree to which the intervention steps are followed and training content is covered	Month 7 (baseline), month 26 (project end)	Research staff; 10 min
Behavioral health training pre-post-test	Survey on the acquisition of knowledge gathered during behavioral health training sessions. Questions are asked before and immediately after each module	Month 6 (baseline)	JJ and BH staff; 5 min per module
Behavioral health training—live sessions fidelity checklist	Documents the degree to which the intervention steps are followed and training content is covered	Month 7 (baseline)	Research staff; 10 min per session
Goal achievement training fidelity checklist	Documents the degree to which the intervention steps are followed and training content is covered	Month 7 (baseline)	Research staff; 10 min
Goal achievement training pre-post-test	Survey of best practices for determining and defining goals, identification of site-selected goals along the Cascade, strategies for measuring progress toward goals, strategies for implementing and sustaining change	Month 7 (baseline)	JJ and BH staff; 10 min
Enhanced components (Enhanced condition only)			
Pre-implementation fidelity checklist	Documents the degree to which preparations for facilitation are followed	Month 8 (experiment)	RC facilitator; 10 min
Local change team (LCT) start-up fidelity checklist	Documents the degree to which plans for establishing LCTs and initiating facilitation are followed	Month 8 (experiment)	RC facilitator; 10 min
Meeting level facilitator reflection fidelity checklist (RC facilitator and local champion versions)	Documents the degree to which the facilitation protocol is followed and LCT discussions/progress toward goals	Month 8-19 (experiment)	RC Facilitator and Local Champion; 10 minutes per meeting
LCT fidelity checklist	Survey of LCT members regarding facilitation of their meetings	Months 8, 13, and 19 (experiment)	LCT; 10 min
Close-out meeting fidelity checklist	Documents the degree to which the close-out meeting plans are followed (including study debriefing)	Month 26 (at conclusion of post-experiment)	Research staff; 10 min
DATA COLLECTION			
Extraction of youth service records			
Community supervision survey	A subset of the JJ-TRIALS National Survey items (JJ version) used to elicit site characteristics and information about services provided	Month 1 (baseline), month 20 (sustainment)	JJ agency leadership; 2 h
Service provider survey	A subset of the JJ-TRIALS National Survey items (service provider version) used to elicit site characteristics and information about services provided	Month 1 (baseline), month 20 (sustainment)	BH agency leadership
Monthly site check-in form	Documents site activities that reflect progress toward achieving selected goals, collect information about process improvement efforts, and monitor changes to services based on data systems, staffing, and policy modifications	Months 8–25 (experiment, post-experiment)	Research staff interview site liaison; 30 min, monthly
Staff survey	The survey asks individuals about attitudes toward their workplace, services their agency provides, relationships between JJ and BH agencies in providing services, perceived value and use of substance use services (specific strategies for screening, assessment, referral, and treatment), and perceived value of HIV-STI and substance use prevention	Month 5 (baseline), months 9 and 19 (experiment), month 25 (post-experiment)	JJ and BH staff; 45 min, each administration

#### Fidelity

The JJ-TRIALS cooperative seeks to manage fidelity by balancing adherence to central elements of the implementation interventions and timely submission of research data with flexibility in addressing diverse site needs. This approach to fidelity aims to address the domains described by Proctor and colleagues [67] with regard to protocol adherence, dose/exposure, and quality. Protocol adherence is fostered by the provision of pre-implementation training activities to key principals (e.g., facilitators) along with the review of critical resources (e.g., detailed instructional manuals, preparation checklists). As implementation ensues, fidelity is further measured by RC-level reporting of the actual date of each study activity relative to its targeted completion date. The Timeline Compliance system tracks key elements of dose, such as the number of attendees at specific trainings [44]. Each implementation intervention has fidelity procedures that provide additional detail regarding adherence, dose, and quality. Procedures include automated reporting (e.g., online BH training sessions), observational ratings (e.g., webinar BH training sessions), facilitator-reported fidelity ratings (e.g., goal achievement training), and participant ratings (e.g., local change team meetings).

### Hypotheses

Table 3 summarizes the primary hypotheses corresponding to the research questions above. H1 and H2 focus on retention in the Cascade: H1 compares both experimental conditions to their respective baseline period, whereas H2 compares the differential effectiveness of Core versus Enhanced sites. Table 3 shows the working definition and formula for the rates of each step within the Cascade (see Fig. 1), designed to map onto existing and widely used performance metrics systems (Center for Substance Abuse Treatment adolescent treatment branch and National Outcome Monitoring System; the Network for the Improvement of Addiction Treatment (NIATx); the National Quality Forum; the Office of National Coordinator of Healthcare Reform; and Washington Circle Group). The rates shown are proportions of youth receiving the service within each site, divided by the number in the earlier step, with dashed lines highlighting changes in the denominator.

**Table 3 Tab3:** JJ-TRIALS research questions and hypotheses

Primary research question	Corresponding hypotheses
1. Does the Core and/or Enhanced intervention reduce unmet need by increasing service cascade retention related to screening, assessment, treatment initiation, engagement and continuing care?	*H1:* Compared to baseline period, the percentage of *youth retained in the service cascade* will increase during the experiment period (in terms of % screened, % assessed, % in need, % referred, % initiated, % engaged, and % continuing care).
2. Does the addition of the Enhanced intervention components further increase the percentage of youth retained in the service cascade relative to the Core components?	*H2:* Compared to the Core intervention sites, the Enhanced Intervention sites will have greater improvements (relative to baseline) during the experiment period in their percentage of *youth retained in the service cascade* (in terms of % screened, % assessed, % in need, % referred, % initiated, % engaged, and % continuing care).
3. Does the addition of the Enhanced intervention components improve service quality relative to Core sites?	*H3:* Compared to the Core intervention sites, the Enhanced intervention sites will have greater improvements (relative to baseline) during the experiment period in service quality in terms of:
	a) *timing* (e.g., shortened length of time between arrest and screen),
	b) *content* (e.g., increased use of EBP to screen), or
	c) *procedure* (e.g., increased number of staff trained on using an EBP screener).
	(NOTE: H3b & H3c are largely descriptive and exploratory.)
4. Do staff perceptions of the value of best practices increase over time, and are increases more pronounced in enhanced sites? [staff within sites]	*H4:*
	*a)* Relative to Staff at the Core sites, staff at Enhanced sites will show a greater increase between baseline and end of experimental period in the perceived “value” and reported use of *evidence-based substance use treatment services* along the Cascade.
	b) Staff in both Core and Enhanced sites will show an increase between baseline and end of core support period in the perceived “value” of *HIV/STI prevention, testing, and treatment services*.
	c) Staff in both Core and Enhanced sites will show an increase between baseline and end of core support period in the perceived “value” of *evidence-based substance use prevention services*.

Latent Growth Curve Modeling (LGCM) will be used to test H1 and H2 using MPLUS [68]. A significant change in the slope between the baseline and experimental time periods (H1) or between Core and Enhanced conditions (H2) would suggest that the intervention affected the growth curve. This analysis will be repeated for each targeted outcome measure in the Cascade. To the extent that there are site differences, data can be analyzed within sites, using non-parametric simplified time series (STS) analysis [69, 70]. MPLUS will also allow examination of time-varying covariates to determine whether early implementation activities have significant effects on later time points.

H3a utilizes bi-weekly intake cohorts and tests whether percentages of youth meeting “timing targets” differ significantly between the 18 Enhanced and the 18 Core sites. Records data include dates to allow examination of time between various points in the Cascade (see Table 4). Trends can be examined over time using simplified time series analysis. H3b and H3c are considered exploratory, using data from agency surveys and needs assessment group interviews (measured twice: baseline and end of experiment; see Table 5). Survey content is derived from the JJ-TRIALS National Survey (developed by Chestnut Health Systems and administered in 2014). Group interviews (recorded and transcribed) generate descriptive detail on the entire Cascade, including system capacities, referral processes, the nature and use of screening instruments, the quality of available services, and features in the inner and outer contexts of agencies likely to influence service delivery.

**Table 4 Tab4:** Measures from de-identified records corresponding to the Behavioral Health Service Cascade

Step	Operational definition	Rate
a. JJ referrals	Total number of referrals to juvenile justice in time period with a disposition start date, less any youth already in treatment at that time	–
b. Screened	Subset of JJ referrals (a) with a screening date	b/a
c. Clinical assessment	Subset of JJ referrals (a) with a full clinical assessment (includes if follow-up to screening or other clinical assessment)	c/a
d. Need identified	Subset of JJ referrals (a) with a need for substance use treatment based on screener, urinalysis, clinical assessment, or other sources of information	d/a
e. JJ Referrals to treatment	Subset of those in need (d), referred by the juvenile justice system to substance use treatment	e/d
f. Initiated treatment	Subset of those referred to treatment (e) who have treatment start date	f/e
g. Engaged in treatment	Subset of those who initiate treatment (f) who stay in treatment for at least 6 weeks (based on treatment discharge minus treatment start date)	g/f
h. Continuing care	Subset of those engaged in treatment (g) that are still getting treatment after 90 days (whether via retention, transfer or booster)	h/g

**Table 5 Tab5:** Service cascade: crosswalk of quantitative and quality measures

	Example measures of quality		
Service cascade measure	Timing	Content indicators	Procedural indicators
Substance use screening	Days between JJ intake and screening (target: within 30 days of intake)	Use of a psychometrically sound screening instrument	Training and quality assurance provided to staff
		Use of 2 or more sources of corroborating evidence when screening	Screening results used to inform referral to full clinical assessment and/or treatment
Full clinical assessment	Days between JJ intake and assessment (target: within 30 days of intake)	Use of a psychometrically sound clinical instrument	Training and quality assurance provided to staff on administration and interpretation of assessment
		Use of DSM criteria	Assessment results used to inform placement plans
		Use of two or more sources of corroborating evidence when assessing	Qualifications of staff doing assessment
Determination of substance use-related need	Days between screen/assessment and determination of need (target: 14 days)	Determined by a psychometrically sound screening or assessment instrument	Documentation of need in record/service plan
			Communication of needs across system (e.g., judge, probation officer)
Treatment referral	Days between determined need and treatment referral (target: 14 days)	Quality of services (e.g., provider is accredited)	Treatment program contact information provided
		Match between client needs and service intensity	Active referral (e.g., phone call made; transportation provided)
Treatment initiation	Days between treatment referral and first session (target: 30 days)	Use of evidenced-based treatment approach	Documentation of first session (confirmed by service agency)
Treatment engagement	Remaining in treatment for at least 6 weeks (i.e., time from treatment intake to discharge is greater than 42 days)	Minimum education requirement of staff providing treatment services	Documentation of multiple sessions (confirmed by service agency)
		Treatment completion/discharge status	
Continued care	Receiving any treatment session after 90 days of treatment	% of youth continuing in any care	Documentation of continued attendance (confirmed by service agency)
		Number of days in continuous treatment	
	Number of continuous treatment sessions		
		Retention/dosage within each episode	
		Service intensity across episodes (increasing, decreasing)	

H4 examines staff perceptions of the value of services along the Cascade. Table 6 describes domains and sample items. Analyses will focus on change in staff responses cross-sectionally over time, using staff nested within agency. Hierarchical linear modeling (HLM) [71] will serve as the basic analysis paradigm in which Enhanced and Core sites are compared. Growth modeling may be appropriate since measures will be collected approximately every 6 months, and it is expected that the groups will be equivalent at baseline. MPLUS can be used to analyze these data using “known class” as an indicator of implementation condition in a multigroup analysis (e.g., linear growth curve modeling). Time-invariant and time-varying covariates that may differentially affect the growth curves of the two implementation conditions will be examined. Should growth model specification not fit the data, multilevel regression modeling will be used.

**Table 6 Tab6:** Staff survey domains and example items

Domain	Stem and Example Items	# Items
Primary Research Question: Perceptions of Value and Use of Practices		
Substance Use Services - Resources		
Necessary Resources^a^	I have the right tools to identify substance use needs in the youth on my caseload.	9
Agency Norms^a^	My agency plays an important role in linking youth to substance use services.	4
Substance Use Services - Importance and Use	How important are the following to YOU? --	
	How often are the following USED with justice-involved youth on your Caseload? --	
Screening^b,c^	Screening youth for substance problems.	14
Assessment^b,c^	Conducting a comprehensive assessment of substance use and related problems.	18
Referral to Treatment^b,c^	Referring the youth with a substance problem to treatment services.	26
Treatment^b,c^	Encouraging every youth with a substance problem to initiate treatment services.	18
HIV/STI and Substance Use Prevention Services – Importance	How important are the following to YOU? --	
HIV/STI Prevention^b^	Educating youth about safe sex practices.	4
HIV/STI Testing^b^	Recommending that all youth be tested for HIV as part of their service plan.	7
HIV/STI Treatment^b^	Promptly linking youth with HIV seropositive test results to HIV treatment services.	8
Substance Use Prevention^b^	Strengthening youth anti-drug use attitudes, beliefs, and norms.	6
Exploratory Research Question: Implementation Process and Data Use		
Youth Data - Importance and Use [77]		
Performance Expectancy^a^	Using youth data can be helpful for -- assessing whether needs of youth are being met.	5
Social Influence^a^	The senior management of this agency promotes use of youth data to inform decisions.	2
Facilitating Conditions^a^	I have the resources necessary to use youth data to inform decisions.	3
Anxiety^a^	I feel confident about using youth data to inform decisions.	3
Intention to Use^a^	In the next 3 months -- I predict I will use youth data to inform decisions.	2
Domain	Stem and Example Items	# Items
Individual Use^d^	Within the past 3 months -- I have used youth data to assess whether needs of youth are being met.	5
Implementation Process Strategies - Importance^b^	How important is each of the following when your agency is changing a policy, process, or procedure? -- Involving an interagency workgroup that includes representatives from both juvenile justice and behavioral health providers.	10
Exploratory Research Question: Inter-agency Collaboration		
Inter-organizational Relationship [78]		
Resource Exchanges^d^	To what extent does your agency -- send results from screening youth for alcohol or drug problems to < <your partner agency> > ?	6
Resource Needs^e^	To attain your agency’s goals, to what extent does your agency need services, resources, or support from < <your partner agency> > ?	3
Challenges to Collaboration^e^	To what extent is your agency’s relationship with < <your partner agency> > hampered by -- concerns about youth confidentiality and release of information?	6
Effectiveness of Relationship^e^	To what extent does < <your partner agency> > carry out commitments it agreed to with your agency?	4
Agency and Personal Awareness^e^	To what extent -- does your agency collaborate with < <your partner agency> > in planning delivery of services to youth?	3
Quality of Communications^e^	When you wanted to communicate with persons in < <your partner agency> > during the past six months, -- how much difficulty have you had in getting in touch with them?	4
Frequency of Communications^f^	During the past six months, how frequently have you -- sent or received material (of any kind) by mail, courier, or fax with anyone in < < your partner agency> > ?	4
Exploratory Research Question: Inner Context as Moderators of Implementation Effectiveness		
Structural Characteristics of the Organization	Staff size and diversity, caseload, client census, client composition (i.e., characteristics of juveniles on supervision), accreditation, etc.	18
Organizational Climate [79]		
Innovation/Flexibility^g^	New ideas are readily accepted here.	6
Domain	Stem and Example Items	# Items
Performance feedback^g^	People usually receive feedback on the quality of work they have done.	5
Quality^g^	This organization is always looking to achieve the highest standards of quality.	4
Organizational Support^g^ [80]	This organization really cares about my well-being.	8
Organizational Functioning [81]		
Communication^a^	Staff members always feel free to ask questions and express concern.	6
Stress^a^	Staff members are under too many pressures to do their jobs effectively.	4
Satisfaction^a^	You are satisfied with your present job.	6
Adaptability^a^	You are willing to try new ideas even if some staff members are reluctant.	4
Encourages Innovation^a^	Your supervisor encourages staff to try new ways to accomplish their work.	4
Organizational Needs^a^	Your organization needs additional guidance in -- assessing youth needs.	7

Note: Scale Range: ^a^Disagree strongly, Disagree, Neither disagree nor agree, Agree, Agree strongly; ^b^Not important, Slightly important, Moderately important, Important, Very important; ^c^Not used, Some-times, Half the time, Most times, All the time; ^d^Never, Rarely, Occasionally, Frequently, Very Frequently; ^e^Not at all, A little bit, Somewhat, A fair bit, Very much; ^f^Zero times, 1 time, About 2 times, About 3 times, About every month, About every two weeks, About every week, About every 2-3 days, About every day; ^g^Definitely false, Mostly false, Mostly true, Definitely true

